##### Cardiorespiratory fitness

2.7.2.2

Cardiorespiratory fitness (ie, maximum oxygen consumption [VO_2máx_]) will be estimated through the Siconolfi Step Test. This test has been developed for use in epidemiological studies^[55]^ and has been used in different populations.^[55–58]^ The test is performed on a wooden box (25.4 cm × 30.5 cm × 45.7 cm) made ad hoc. Heart rate (HR) is monitored using a HR monitor (Polar V800; Polar Electro, Kempele, Finland). In stage 1, the participant has to step up and down the box at a frequency of 17 times per minute for 3 minutes. If the average HR of the participant during the last 30 seconds of stage 1 reaches or exceeds 65% of the estimated maximal heart rate (HRmax), the test finalizes. Otherwise, the participant rests for one minute and undetakes stage 2, increasing the step frequency to 26 times per minute for 3 minutes. If the HR criteria is not met in the last 30 seconds of stage 2, stage 3 takes place increasing the step frequency to 32 times per minute for 3 minutes. In this way, the VO_2máx_ is estimated using the following expression^[55,59]^:
 

According to the original protocol, if 65% of the estimated HRmax is reached or exceeded during the stage 1, the round factor is 16.287, whereas the round factor is 24.910 and 35.533 if the 65% of the estimated HRmax is reached in stage 2 or 3, respectively.

##### Shoulder mobility

2.7.2.3

The range of shoulder flexion in supine position will be assessed through digital goniometry (HALO Digital Goniometer; HALO Medical Devices HQ, Sydney, Australia) as reported elsewhere.^[60]^

##### Physical disability of the upper limb

2.7.2.4

Physical disability of the upper limb will be assessed with the Spanish version^[61]^ of the Disabilities of the Arm, Shoulder, and Hand (DASH) questionnaire.^[62]^

##### Cancer-related quality of life

2.7.2.5

Cancer-related quality of life will be assessed with the Spanish version^[63]^ of the European Organization for Research and Treatment of Cancer Quality of Life Questionnaires-Core30 (EORTC QOL-30),^[64]^ including the Spanish version^[65]^ of the extension for breast cancer (EORTC QLQ-BR23).^[66]^ The global score ranges from 0 to 100 where higher scores indicate better quality of life. Cancer specific quality of life will also be assessed with the Spanish version^[67]^ of the Functional Assessment of Cancer Therapy-Breast (FACT-B)^[68]^. The global score ranges from 0 to 148 where higher scores indicate better quality of life.

##### Cancer-related fatigue

2.7.2.6

Cancer-related fatigue will be assessed with the Spanish version^[69]^ of the Functional Assessment of Cancer Therapy-Fatigue (FACT-F)^[70]^ questionnaire.

##### Depressive symptoms

2.7.2.7

Depressive symptoms will be assessed with the Spanish version^[71]^ of the 20-item for Epidemiologic Studies-Depression Scale (CES-D)^[72]^

##### Life satisfaction

2.7.2.8

Life satisfaction will be assessed with the Spanish version^[73]^ of the satisfaction with life scale (SWLS).^[74]^

##### Anthropometrics and body composition

2.7.2.9

Weight (in kg) and body composition (including body fat percentage, fat-free mass [kg], etc) will be assessed with a bioelectrical impedance device (InBody 120; InBody Co Ltd, Seoul, Korea) and height will be measured with a digital stadiometer (Seca 202; Seca Ltd, Hamburg, Germany). Hip and waist circumference will be measured with an anthropometric tape (Seca 201; Seca Ltd). Body mass index (kg/m^2^), waist-to-height ratio, and waist-to-hip ratio, will be calculated.

##### Arm volume and lymphedema

2.7.2.10

Arm volume and lymphedema will be evaluated by measuring the perimeter of the arm at different points that will be 6 cm apart, to estimate the volume of both arms using the following expression^[75]^:
 

where n = number of segments, *L* = length of each segment, and *C*_*i*_ and *C*_*i*−1_ = circumference at each end of the segment. Subsequently, both volumes will be compared, and the presence of lymphedema will be considered when the volume of the affected arm exceeds the volume of the non-affected arm by 3-10%.^[76–78]^

### Data collection procedure

2.8

Baseline (ie, from September 9 to September 20, 2019) and follow-up (from December 16 to December 20, 2019) evaluations will be performed at the Exercise Laboratory of the University of Almería. Each participant begins filling out online questionnaires including health-related quality of life, cancer-related fatigue, depression, life satisfaction, and a general sociodemographic questionnaire. Thereafter, body composition is assessed in a private room, followed by shoulder joint mobility and presence of lymphedema, upper- and lower-body muscular strength and cardiorespiratory fitness.

### Statistical analysis

2.9

The distribution of the main study variables will be assessed through histogram and Q-Q plots. Descriptive characteristics will be presented using the mean and standard deviation for normally distributed quantitative variables, the median and interquartile range for non-normally distributed quantitative variables, and the number and frequency for categorical variables. The comparability of the groups will be checked at baseline and potential confounders that present baseline group differences will be included in the analyses. The between-group differences in the primary and secondary outcomes will be assessed through linear or quantile regression, as appropriate. As we aim at assessing efficacy, the primary analyses are defined as per-protocol, where participants from the exercise group will be included if their attendance to the exercise sessions is ≥75%. Sensitivity analyses will also be carried out using a minimum attendance of ≥90% and using the intention-to-treat principle. Blinded investigators ([name] and [name]) will handle all hypothesis testing. The main analyses will be conducted with Stata v.13.1 (StataCorp LP, College Station, TX). Statistical significance will be set at *P* < .05.

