### Sample size

2.4

The sample size was calculated for the primary outcome (ie, muscular strength) using Stata v.13 (StataCorp LP, College Station, TX). Based on the results of the meta-analysis by Strasser et al,^[23]^ a difference in the change between groups in lower limb muscle strength of at least 6.9 kg would be clinically relevant. Assuming a common standard deviation of 7.5 kg, a 90% power, an alpha error of 5%, and considering a potential dropout of 20%, we will aim at enrolling 60 participants.

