### Outcome measures

2.7

All outcome measures will be assessed at baseline and at week 12 (ie, after concluding the intervention period). Baseline assessment will be carried out during the 14 days before the beginning of the intervention and follow-up assessments will be conducted in the following 10 days from finalizing the intervention. The principal investigators ([name] and [name]) are responsible for the dataset and will only distribute it between trial investigators who are included in the funded project.

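### Covariates are chosen by observed baseline differences and the regression type is left open, so the primary model is data-driven and need not include baseline strength; the cost is about 1 to 5 points of power

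*Protocol article*

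**What the plan says.** The Statistical analysis section (2.9) of the protocol article makes two choices depend on the data.

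- **Covariates.** Groups are compared at baseline, and then "potential confounders that present baseline group differences will be included in the analyses". No variables are listed and no criterion for a difference is given.
- **Model.** "The distribution of the main study variables will be assessed through histogram and Q-Q plots", and the between-group differences "will be assessed through linear or quantile regression, as appropriate". No rule for choosing is stated, and no quantile is named.

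The Outcome measures section (2.7) says: "All outcome measures will be assessed at baseline and at week 12". Baseline strength is therefore available for every participant, but section 2.9 does not make it a fixed model term. Section 2.9 also does not say whether the dependent variable is the week-12 value or the change. The only form of the contrast given anywhere is in Sample size (2.4): "a difference in the change between groups in lower limb muscle strength of at least 6.9 kg would be clinically relevant".

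**The concern.** A covariate improves the estimate to the extent that it predicts the outcome. Whether it happens to differ between the arms is a poor guide to that. Under the printed rule a weak predictor can enter because it is imbalanced, while baseline strength, which is likely to be the best predictor of later strength, can be left out because it is balanced. With three primary strength scores, each could end up with a different model.

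The open choice of regression adds to this. Linear regression estimates a difference in means; quantile regression at the median estimates a difference in medians. If the choice follows inspection of the distributions, the quantity being estimated is settled after the data are seen. Linear regression does not need a normally distributed outcome to be valid, so a non-normal histogram is not in itself a reason to switch.

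At stake are precision in a trial of 60 women and a primary model that is not fixed in advance.

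**Working it through.** **Inputs from section 2.4.** Difference 6.9 kg, SD 7.5 kg ("Assuming a common standard deviation of 7.5 kg"), power 90%, alpha 5%, dropout 20%, N = 60. **Assumptions.** Two-sided test; 1:1 allocation; 7.5 kg is the SD of the change; the baseline to week-12 correlation ρ, which the article does not give, lies between 0.5 and 0.9; a baseline difference means p < 0.05.

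**1. The plan's own figure.** n per arm = 2 × [7.5 × (1.960 + 1.282) / 6.9]² = 24.8, rounded up to 25, so 50 in total. 50 × 1.2 = 60, which matches. If 20% of the 60 drop out, 48 remain, 24 per arm.

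**2. Unadjusted change with 48 completers.** Standard error = 7.5 × √(2/24) = 2.165. 6.9 / 2.165 − 1.960 = 1.227, which gives power 89.0% (87.7% by the t-test).

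**3. Fixed analysis of covariance (ANCOVA) on baseline strength.** With a common SD σ of single measurements, change has variance 2σ²(1 − ρ) and ANCOVA has residual variance σ²(1 − ρ²). The ratio is (1 + ρ)/2, so the effective SD is 7.5 × √[(1 + ρ)/2]. At ρ = 0.7 that is 6.91 kg, and power is 93.3%.

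**4. The printed rule, applied to baseline strength.** Simulation with 24 per arm and 5,000 trials per setting: analyse change unadjusted, but switch to ANCOVA when baseline strength differs at p < 0.05.

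| ρ | ANCOVA SD (kg) | ANCOVA power, formula | Rule, simulated | ANCOVA, simulated | Loss (points) |
|---|---|---|---|---|---|
| 0.5 | 6.50 | 95.7% | 89.1% | 94.2% | 5.1 |
| 0.7 | 6.91 | 93.3% | 88.6% | 92.0% | 3.4 |
| 0.8 | 7.12 | 91.9% | 88.2% | 90.9% | 2.7 |
| 0.9 | 7.31 | 90.5% | 87.8% | 88.8% | 1.0 |

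The simulation error of one power figure is about √(0.88 × 0.12 / 5,000) = 0.5 points, so the loss at ρ = 0.9 is small and imprecise.

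**5. Type I error of the rule on change.** 3.9%, 4.6%, 4.7% and 5.4% at the four correlations: close to nominal.

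**6. Linear or median regression under the null.** With 1,000 trials per setting and a normality test as the gate, the rejection rate was 4.9% on normal data and 3.1% on skewed data. Always taking the smaller p-value gave 5.5% and 6.3%, with simulation error of about ±1.4 points.

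**The case against.** Several points on the other side have force.

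*Baseline differences may be more than chance.* The primary analysis is per-protocol: exercise-arm women count only with at least 75% attendance, and controls face no matching restriction. Differences in that set can be systematic, so concern about confounding is legitimate. This stands. It rules out the argument that every baseline difference is random, and it argues against a very short covariate list. It does not rescue selection by observed imbalance, since confounders can be named beforehand. The simulation uses fully randomised arms and does not model this selection.

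*The rule does protect somewhat.* Among simulated null trials with a baseline difference at p < 0.05, unadjusted change rejected 9% to 13% of the time and ANCOVA 4% to 7% (about 250 trials per setting, so rough). The rule adjusts in exactly those trials. Fixed ANCOVA gives the same protection and gains precision in the rest.

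*Blinded investigators do the testing.* That limits choosing a model for its result. It does not fix the model.

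*The plots may serve only the descriptive tables.* The text does not link them to the regression choice. That they drive it is an inference, though the natural one.

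A reader might also infer more than the documents support:

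- **Inflated type I error.** Not shown. The rule is near nominal on change and conservative, at 2.2% to 4.7%, on week-12 values.
- **A large power loss.** If raw week-12 values were analysed, with single-measurement SD 7.5/√[2(1 − ρ)], the rule would give 87.9%, 68.9%, 52.8% and 31.1% power at ρ = 0.5, 0.7, 0.8 and 0.9, against 94.1%, 91.8%, 90.6% and 88.8% for ANCOVA. The article nowhere says that raw week-12 values are the outcome, and its one stated contrast is in change.
- **A heavy cost from median regression.** On normal data its efficiency of 2/π would lower power from 89.0% to 72.0%. On normal data, however, this plan would presumably choose linear regression.
- **A near-certain spurious covariate.** Any such probability needs a number of variables, a test and a threshold, and the article gives none.

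**Conclusion.** The concern holds in a limited form. Section 2.9 states a selection rule with the wrong criterion and leaves the regression type open. This is a rule badly fixed in print, not detail that a separate analysis plan would normally supply: a plan that followed it would inherit the fault, and one that fixed the model would contradict it.

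The size is modest: 1 to 5 points of power on the change contrast. That rests on the assumed correlation range, on 48 women in the analysis (the per-protocol set could be smaller) and on carrying the lower-limb effect in kg (6.9/7.5 = 0.92 SD) over to primary outcomes that are averaged z-scores. ANCOVA had the higher power in every setting computed for correlations of 0.5 to 0.9. The other harm, a primary model not settled beforehand, does not depend on these assumptions. It should be fixed, but it does not threaten the trial.

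**What to change.** Replace the covariate and model sentences of section 2.9, and the matching text of any analysis plan, before unblinded data are examined:

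- Delete the selection of covariates by baseline difference. Baseline characteristics can still be tabulated.
- Analyse each continuous outcome by linear regression of the week-12 value on group and the same outcome at baseline, with robust or bootstrap confidence intervals.
- Add a short list of covariates named now on prognostic grounds.
- For the per-protocol analysis, also name in advance the variables likely to predict attendance, and do not cap that list at one or two.
- Keep median regression as a sensitivity analysis.

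The baseline values are already being collected. The cost is a change of wording and a few degrees of freedom.

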**Methods::**

This study is a parallel-group randomized controlled trial in which 60 female breast cancer survivors, who have completed central treatments of the disease in the last 5 years, will be randomly assigned to either an experimental group that will perform a total of 24 progressive resistance training sessions for 12 weeks (ie, 2 weeks of individual training and 10 weeks of micro-group training) and will be requested to undertake 10,000 steps/d, or a control group that will be requested to undertake 10,000 steps/d, only. Outcomes will be evaluated at baseline and at week 12. Primary outcome measure is peak isometric muscular strength of the lower- and upper-body, assessed with several exercises through an electromechanical dynamometer. Secondary outcomes include cardiorespiratory fitness, upper-joint mobility and disability, health-related quality of life, cancer-related fatigue, depression, life satisfaction, and presence of lymphedema.

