The primary aim of this study is to assess the effect of a 12-week supervised resistance exercise program combined with home-based aerobic training, compared with home-based aerobic training only, on muscular strength in breast cancer survivors. Secondary aims are to assess the effects of the intervention on cardiorespiratory fitness, upper-limb mobility and disability, health-related quality of life, cancer-related fatigue, depressive symptoms, life satisfaction, body composition, and lymphedema in this population.

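### Presence of lymphedema has no single cut-off, and the plan does not commit to the baseline-adjusted arm-volume difference that it could analyse at almost no cost (minor; one secondary outcome)

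*Protocol article*

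**What the plan says.** Lymphedema is among the secondary aims at the end of the Introduction: "life satisfaction, body composition, and lymphedema in this population". The abstract's list of secondary outcomes gives it as presence: "cancer-related fatigue, depression, life satisfaction, and presence of lymphedema". Section 2.8, on the order of testing, does the same: "shoulder joint mobility and presence of lymphedema".

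Section 2.7.2.10 covers both volume and diagnosis: "Arm volume and lymphedema will be evaluated by measuring the perimeter of the arm at different points". It estimates the volume of each arm and then sets the case definition: "the presence of lymphedema will be considered when the volume of the affected arm exceeds the volume of the non-affected arm by 3-10" per cent. No single value in that range is chosen.

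Section 2.7 fixes the timing: "All outcome measures will be assessed at baseline and at week 12". Section 2.9 gives one rule for all outcomes: "The between-group differences in the primary and secondary outcomes will be assessed through linear or quantile regression, as appropriate". Its only stated covariate rule is that "potential confounders that present baseline group differences will be included in the analyses". The outcome's own baseline value is not mentioned. Section 2.2 does not exclude women who already have lymphedema.

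**The concern.** A case definition given as a range cannot be applied as one rule. Someone must choose a value between 3 and 10%, and nothing in the text says that this happens before the data are seen. Read literally, the range is even a band, and women above 10%, the clearest cases, would fall outside it.

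The label is also the less informative form of what is measured. Both arm volumes are available at both visits, but a yes/no status at week 12 keeps only which side of the cut-off a woman is on. It also counts women who were already cases at baseline. At stake is how clear and how precise the result is for one secondary aim.

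**Working it through.** **Inputs from the protocol article.** Section 2.4 gives 60 women and 20% dropout. With equal arms (assumed), 60 × 0.80 / 2 = 24 evaluable per arm. The article gives no figure for lymphedema. The 60 was set for strength and reproduces: 2 × (7.5 × (1.960 + 1.282) / 6.9)² = 24.8, so 25 per arm; 25 × 1.20 × 2 = 60.

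**Assumed inputs, none in the article.** The percentage inter-arm volume difference is normal with mean 2 and SD 5. The true effect is 2 points, with the exercise arm higher. The baseline to week-12 correlation r is 0.6, 0.8 or 0.9. Tests are two-sided at 5%.

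**Step 1: what the cut-off does.** Prevalence at cut-off c is 1 − Φ((c − mean)/SD).

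| Mean, SD | c = 3% | c = 5% | c = 10% | Cases at 3% that are not cases at 10% |
|---|---|---|---|---|
| 2, 5 | 42.1% | 27.4% | 5.5% | 1 − 0.055/0.421 = 87% |
| 0, 4 | 22.7% | 10.6% | 0.6% | 97% |
| 4, 8 | 55.0% | 45.0% | 22.7% | 59% |

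Read as a band from 3 to 10%, the first row gives 42.1 − 5.5 = 36.6%, and the 5.5% of women above 10% would count as non-cases.

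**Step 2: power of the week-12 label.** The rates by arm are 42.1 v 57.9% at cut-off 3, 27.4 v 42.1% at 5, and 5.5 v 11.5% at 10. Linear regression of the 0/1 label on arm, enumerated over all possible tables with 24 per arm, has power 22%, 19% and 10%.

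**Step 3: power of the continuous analyses.** The standard error is SD* × √(2/24) = 0.2887 × SD*. Power comes from the noncentral t distribution with noncentrality 2/SE.

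- Week-12 volume difference, unadjusted: SD* = 5, noncentrality 1.39, power 27%.
- Change from baseline: SD* = 5√(2(1 − r)).
- Week-12 value adjusted for baseline: SD* = 5√(1 − r²).

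| r | Change: SD* | Change: power | Adjusted: SD* | Adjusted: power | Gain (points) |
|---|---|---|---|---|---|
| 0.6 | 4.47 | 33% | 4.00 | 40% | 7 |
| 0.8 | 3.16 | 57% | 3.00 | 62% | 4 |
| 0.9 | 2.24 | 86% | 2.18 | 88% | 2 |

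Gains are taken before rounding. In 20,000 simulated trials per setting, the adjusted analysis gave 39, 61 and 86%, and its type I error was 0.049 to 0.051.

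**Step 4: pre-existing cases.** With no treatment effect and r = 0.6, 0.8 and 0.9, the share of week-12 cases that were already cases at baseline is 66, 76 and 83% at cut-off 3%, and 32, 50 and 65% at cut-off 10%.

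**The case against.** The strongest reply is that calling presence the outcome rests on shorthand in the abstract and in a sentence about test order. The section that defines the measure is headed with arm volume as well as lymphedema, and the regression models in section 2.9 suit a quantitative outcome. This stands: a reader might infer that the plan discards the volume data, but the text leaves a continuous analysis open. What remains is that it does not commit to one.

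A second reply is that a baseline covariate is normally left to an analysis plan, which is not shown. Taken alone, that silence would be no finding. It is raised here only as part of a better method that uses data already collected. The range in the case definition is different, because the article itself states it.

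Third, section 2.4 frames the strength effect as a difference in change between groups, so change scores are a plausible plan for lymphedema too. Against change scores the gain is small, as Step 3 shows.

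Two stronger readings fail. A reader might infer that the named models are invalid for a yes/no outcome. Linear regression of the label gives a valid risk difference: its exact type I error is 0.018 to 0.060 at rates of 5 to 50%. Section 2.9 says the model is chosen as appropriate, so nothing indicates that quantile regression would be used on the label. A reader might also infer that pre-existing cases bias the comparison. Randomization balances them in expectation, so they cost precision only.

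**Conclusion.** The point holds as a cheap improvement to one secondary outcome. The firm part is the case definition: a range of 3 to 10% is not a threshold, and under the assumed distributions 59 to 97% of cases at the lower end are not cases at the upper end. The second part is a missed opportunity. The plan does not commit to the volume difference or to its baseline value, although both are measured.

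The size of the gain depends on what would otherwise be done: large against the week-12 label, and about 2 to 7 points against change scores. All the lymphedema figures rest on assumed means, SDs, effect and correlations, so they illustrate and do not estimate. The primary strength outcome, the sample size and the conduct of the trial are not affected.

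**What to change.** In section 2.9, state that the main lymphedema analysis is the week-12 percentage volume difference between the affected and non-affected arm, by linear regression on group adjusted for its baseline value, reported with a 95% CI. This needs no cut-off.

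In section 2.7.2.10, choose one cut-off before analysis, defined as at or above a single value with no upper bound. Report presence descriptively by group and baseline status: present at baseline, new, resolved.

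The cost is one or two sentences and one choice, with no new visit, measurement or participant. There are two small downsides. A volume difference is less familiar to clinicians than a prevalence, so the counts should stay beside it. Like the present definition, it also needs one affected and one non-affected arm.

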### Randomization, treatment allocation, and blinding

2.5

After baseline assessment, each participant will be randomized to either an experimental group (EG) or a waiting-list control group (CG). Before participant's recruitment, a blinded investigator ([name]) created a computer-generated simple randomization sequence, to allocate participants in either group. Individual allocations were held in sealed, opaque, and consecutively numbered envelopes. A member of the staff not involved in the trial assessment or interventions will open the envelopes in front of participants and assign them to the groups.

The data analysts and the primary outcome assessors will be blinded to the participant allocation. However, due to the nature of the intervention (ie, supervised resistance exercise), the participants will be aware of the group they are allocated to.

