
**Table 2 T2:**
[figure not shown]
Exercises that are to be performed along the resistance training program^∗^.

All participants will be instructed to report any difficulties, limitations or needs so that the intervention can be adapted to individual needs. To maximize adherence, participants will be sent motivational messages (ie, either through WhatsApp or email) every 2 weeks, and participants who miss sessions will be contacted to ask for reasons and reallocate the schedule to undertake the session another day. Adherence to the program will be reported as the median attendance frequency and the proportion of patients attending ≥75% (ie, 18 sessions; the minimum pre-defined attendance to assess efficacy). Adherence to the exercise program, potential adverse events, and other relevant information will be measured throughout the whole intervention period using a comprehensive tally sheet to be completed daily by the PT during and after each training session. The detailed tally sheet to be used in this study, based on a previous well-designed exercise protocol,^[51]^ is shown as additional file (Table S3). There will not be any nonexercise component in this intervention.

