## Discussion

3

This study will examine the effects of a 12-week supervised resistance exercise program combined with home-based aerobic training, compared with home-based aerobic training only, on muscular strength and health-related quality of life, among other relevant outcomes that are compromised during the treatment follow-up in breast cancer survivors. A number of relevant publications have highlighted that the poor description^[31]^ of exercise programs and the scarce application of training principles in breast cancer clinical trials^[29]^ might explain the inconclusive results in several relevant domains^[36]^ regarding common side-effects of treatment. This study aims at overcoming this relevant issue by presenting a comprehensive description of the supervised resistance exercise intervention that can be replicated and applied in clinical or other settings. Importantly, we follow the CERT guidelines, which should be implemented in all health-related exercise trials. This trial will determine the extent to which a supervised resistance training twice per week improves muscular strength and several relevant outcomes related to quality of life in breast cancer survivors, provided all participants complete the minimum amount of aerobic activity (ie, defined as achieving a minimum of 10,000 steps per day). The results of this relatively small trial will likely be useful for the development of future exercise prescription^[31]^ for breast cancer survivors.

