### Study limitations

3.1

This study has limitations that must be underlined. First, adherence to the exercise programs is a challenge, and several adherence strategies have been incorporated to maximize attendance and motivation. Only women will be enrolled in this study. External validity will not be ensured due to potential selection bias (ie, patients who volunteer to participate may also be the most motivated to exercise). However, the reasons for non-participation and abandonment will be collected and reported.

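### The primary analysis selects the exercise arm on attendance after randomisation, states no matching criterion for controls, and leaves intention-to-treat as a sensitivity analysis

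*Protocol article*

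**What the plan says.** Section 2.9 (Statistical analysis) fixes the primary set: "the primary analyses are defined as per-protocol, where participants from the exercise group will be included if their attendance" is at least 75% of sessions. The reason given is "As we aim at assessing efficacy". Section 2.6.1 (Experimental group) sets the same cut when it describes how adherence will be reported: "the proportion of patients attending ≥75% (ie, 18 sessions; the minimum pre-defined attendance to assess efficacy").

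Section 2.9 names two sensitivity analyses. One raises the attendance cut to 90%; the other is carried out "using the intention-to-treat principle". The only adjustment described is for potential confounders that differ between the groups at baseline.

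For controls, section 2.9 gives no inclusion condition. Section 2.6.2 (Control group) gives them a step goal, monitored by the same bracelet as in the exercise arm, but no analysis set is tied to it.

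**The concern.** Attendance is observed after randomisation, and only exercise women have sessions to attend. Under the stated rule, women who come to fewer than 18 sessions leave the exercise arm. Their counterparts in the control arm, who would have attended poorly had they been assigned to exercise, cannot be identified and stay in. The primary contrast is then attenders against a control group that mixes would-be attenders and would-be non-attenders.

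If the reasons for missing sessions (health, motivation, events during the 12 weeks) also bear on strength at week 12, the two groups differ for reasons other than the training. Adjusting for baseline imbalances cannot be relied on to remove this, because such reasons may arise after baseline or go unmeasured.

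At stake is the trial's main conclusion: the estimate and the test at P < .05 would rest on this selected comparison.

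**Working it through.** **The plan's own figure.** Section 2.4 gives a difference of 6.9 kg, SD 7.5 kg, power 90%, alpha 5% (taken as two-sided) and 20% dropout. Per arm, n = 2 × [7.5 × (1.960 + 1.282) / 6.9]² = 24.83, rounded up to 25. The total is 50, and 50 × 1.2 = 60, which matches the stated enrolment. With 1:1 allocation assumed (section 2.5 states no ratio), that is 30 per arm.

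**Model for the selection.** Suppose there is no true effect. Let each exercise woman have an underlying propensity to attend, normally distributed and correlated ρ with her strength change. The rule drops the lowest fraction f of the exercise arm and none of the controls. The mean of those kept is shifted, in SD units of the change, by

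bias = ρ × φ(z_f) / (1 − f),

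where z_f is the normal quantile at f and φ is the normal density.

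**Assumed inputs.** The article gives neither f nor ρ. I take f = 20% and vary ρ. All 30 controls are taken as analysed, so the comparison is 24 against 30.

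**Results at f = 20%.** z_f = −0.842 and φ(z_f) = 0.280, so bias = ρ × 0.280 / 0.80 = 0.350ρ. The standard error in SD units is √(1/24 + 1/30) = 0.274. The noncentrality is bias / 0.274, and the two-sided type I error follows from the noncentral t with 52 degrees of freedom.

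| ρ | Bias (SD) | Noncentrality | Two-sided type I error |
|---|---|---|---|
| −0.3 | −0.105 | −0.38 | 6.6%, mostly against exercise |
| 0 | 0 | 0 | 5.0% |
| 0.2 | 0.070 | 0.26 | 5.7% |
| 0.3 | 0.105 | 0.38 | 6.6% |
| 0.5 | 0.175 | 0.64 | 9.6% |

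A simulation of 20,000 trials per setting gave 5.8%, 7.0% and 9.6% for ρ = 0.2, 0.3 and 0.5, in close agreement.

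**Other exclusion shares, at ρ = 0.5.** With f = 10%, the bias is 0.10 SD and the simulated type I error 6.5%. With f = 30% they are 0.25 SD and 14.1%, and with f = 40% they are 0.32 SD and 18.4%.

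**The ≥90% set.** Its cut is higher and applies to the same arm, so f can only stay the same or grow. In this model the bias keeps its sign and does not shrink. Agreement between the 75% and 90% sets would therefore not show that selection is absent.

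**Scale.** The primary outcomes in section 2.7.1 are averaged z-scores of tests measured in newtons. The SD-unit results are the ones to read; conversion to kg would apply only to the planning scale of section 2.4.

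**The case against.** The best defence is that the choice is open and prespecified. The threshold is fixed in advance, the reason is stated, and intention-to-treat will be reported alongside. Motivational messages and rescheduled sessions (section 2.6.1) aim to keep the excluded share small. All of this stands as mitigation. It prevents choosing the set after seeing the data, but it does not remove selection from the set that was chosen. An efficacy aim does not make this contrast unbiased either.

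A second defence concerns size and direction, and it largely succeeds. Nothing in the article shows how attendance relates to strength change. Women lost before week 12 have no outcome under intention-to-treat either, so the rule's own effect comes from low attenders who are still tested, and the 5% baseline credits intention-to-treat with complete follow-up.

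A reader might infer more than the article supports:

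- **That every control is kept.** The article only states no criterion for them; controls lost to follow-up would still drop out.
- **That applying the filter breaks the blinding in section 2.5** ("The data analysts and the primary outcome assessors will be blinded to the participant allocation"). Someone outside the analysis could apply it and pass on a file with coded arms. Unequal group sizes need not reveal the arm, because simple randomisation produces them anyway.
- **That section 3.1 admits the problem** where it says "patients who volunteer to participate may also be the most motivated to exercise". That sentence is about who enters the trial, which affects both arms before randomisation.
- **That the Discussion's condition** ("provided all participants complete the minimum amount of aerobic activity") calls for a filter on steps. It describes background activity asked of both arms, and such a filter would add more selection after randomisation.

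**Conclusion.** The point holds. As written, the primary analysis compares a subset of one randomised arm, chosen on behaviour after randomisation, with a control arm for which no matching criterion is stated. Neither the efficacy aim, nor prespecification, nor the ≥90% set repairs that.

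Bias in favour of exercise is likely but not certain, and type I error above 5% is conditional. Both depend on attendance being related to strength change apart from the training. With 20% of the exercise arm excluded, all controls analysed and correlations of 0.2 to 0.5, the bias is about 0.07 to 0.18 SD and the two-sided type I error about 5.7% to 9.6%. These figures illustrate what could happen under assumed inputs; they do not predict this trial's result. The case for change rests on the loss of the randomised comparison in the headline test, whatever the exact size.

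**What to change.** In section 2.9, make intention-to-treat the primary analysis: all randomised women in their assigned arm, with week-12 testing sought from everyone regardless of attendance. Label the ≥75% and ≥90% attendance sets as supportive.

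If efficacy in attenders remains of interest, add a complier-average causal effect estimate with randomisation as the instrument and ≥75% attendance as the exposure. State its assumption about women who attend some sessions but fewer than 18. A step rule for controls is no substitute: it would make the sets look symmetrical without restoring the randomised comparison.

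The cost is a change of wording and order, since both kinds of analysis are already planned and the calculated enrolment of 60 does not change. Following up non-attenders takes some effort. The primary estimate may be somewhat smaller, because low attenders dilute the contrast.
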